### Sample size

Sample size for the study was restricted to the 31 villages in the region available for randomization. Power was estimated using R statistical software across a range of plausible interclass correlation coefficients (ICCs) and absolute changes in follow-up rate from the baseline of 20% in one study arm. Power calculations assumed 15 clusters per study arm with an average size of 70 women per cluster. Power estimates were repeated using a cluster size of 50 women per village with negligible effect. Using these assumptions, we are adequately powered for a 20–30% absolute change in the outcome rate between the study arms, and up to 10% absolute change if low heterogeneity in clusters is found (see Table 4).

**Table 4 Tab4:** Power to detect difference in follow-up simulated across a range of ICCs and effect sizes

ICC	10% absolute increase in follow-up	20% absolute increase in follow-up	30% absolute increase in follow-up
0.01	98%	> 99%	> 99%
0.05	71%	> 99%	> 99%
0.10	47%	95%	> 99%
0.20	28%	75%	98%

A sup-group of women from each arm will complete a follow-up survey to assess cervical cancer screening knowledge retention and patient experience within six months of enrollment. Cluster stratified random sampling was used to select a subset of 25 participants from each cluster to total 375 participants from arm 1 and 400 from arm 2 for this survey. The survey sample size was calculated using a fixed number of clusters [23]; an ICC of 0.5; and assuming a mean knowledge score of 8 in arm 1 and 6 in arm 2 with a coefficient of variation of 1 for this score. Based on these assumptions 25 participants per cluster would result in 83% power to detect this target difference.

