### Statistical analysis

#### Primary objective

Statistical analysis will be performed in R Statistical software using the clusterPower package [28] with an intention to treat approach. The primary outcome rate will be computed for each cluster and each study arm and ICCs calculated to assess cluster level variability prior to the primary analysis. The primary effectiveness measure will be compared between arms by estimating a mixed effect logistic regression model with cluster as a random intercept. The model will be adjusted for all known confounders at the individual and cluster level. There is no planned midpoint evaluation as no serious safety concerns are expected.

Apparent prevalence of HPV and STIs will be estimated in the study regions using trial data. Population prevalence of CIN2+ will be estimated based on this apparent prevalence using the reported sensitivity and specificity of the GeneXpert HPV test for this disease status (Table 5).

**Table 5 Tab5:** Diagnostic test characteristics for moderate and severe cervical lesions

	CIN2+	CIN3
Sensitivity	90.8%(84.7–95.0%)	92.3%(84.8–96.9%)
Specificity	42.6%(38.5–46.9%)	40.0%(36.1–44.0%)

Secondary outcomes compared between arms will be estimated in a similar manner. The effect of each study arm on HPV incidence is estimated using a multi-level logistic regression model as per the primary analysis. The effect of each study arm on CCS knowledge and patient experience will be estimated using a multi-level Poisson model, adjusted for the same individual and cluster level confounders with the addition of HPV status as an individual compounder and with person-time in follow-up as an offset.

Planned secondary analyses include estimating the group by arm interaction of HIV and other STI status on effectiveness of each CCS model. This will be done by adding an interaction term for each comorbidity and arm in the primary model. Temporal trends in HPV incidence and follow-up will be presented graphically.

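### The knowledge survey's stated 83% power does not follow from its printed assumptions, which give about 19%; at least one input or the power is misstated

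*Protocol article*

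**What the plan says.** The second paragraph of the Sample size section describes a survey of knowledge retention and patient experience in a subset of women. The sampling is to "select a subset of 25 participants from each cluster", "to total 375 participants from arm 1 and 400 from arm 2 for this survey", which implies 15 and 16 villages. On method it says "The survey sample size was calculated using a fixed number of clusters", with a literature reference. The remaining assumptions are an ICC of 0.5 and, for the outcome itself, "assuming a mean knowledge score of 8 in arm 1 and 6 in arm 2 with a coefficient of variation of 1". The conclusion drawn from them is that "25 participants per cluster would result in 83% power to detect this target difference". Alpha, sidedness and the test are not given for this calculation.

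Under Statistical analysis, the plan for this outcome is: "The effect of each study arm on CCS knowledge and patient experience will be estimated using a multi-level Poisson model". Knowledge is the first secondary outcome listed for comparison between arms under Study outcomes.

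**The concern.** A coefficient of variation is the standard deviation divided by the mean. A value of 1 for a score with means 8 and 6 makes the standard deviations 8 and 6, so the target difference of 2 is only a quarter to a third of a standard deviation. An ICC of 0.5 is also very large: it makes the women in one village nearly redundant with each other. A difference that small, with clustering that strong and only 31 villages, should not give 83% power.

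The sentence is the only numerical justification in the article for surveying 775 women and for comparing knowledge between arms. A comparison with about 80% power and one with about 19% are read very differently, above all when the result is null. The printed text does not tell the reader which applies. Anyone who reused the printed CV and ICC to plan a similar survey would also be misled.

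**Working it through.** **Inputs (Sample size section):** means 8 and 6, difference 2; CV 1; ICC 0.5; m = 25 women per village; 375 women (15 villages) and 400 women (16 villages). **Assumed, because not stated:** two-sided alpha 0.05, critical value 1.96.

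**Formulas.** Design effect DE = 1 + (m − 1) × ICC. SE = √(V1 × DE/375 + V2 × DE/400), where V1 and V2 are the score variances. Power = Φ(2/SE − 1.96), where Φ is the standard normal distribution function.

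**1. Where the stated 83% can be reproduced.** Keep every printed input except the CV, and set each variance equal to its mean (V1 = 8, V2 = 6):
- DE = 1 + 24 × 0.5 = 13
- SE = √(8 × 13/375 + 6 × 13/400) = √(0.277 + 0.195) = 0.687
- 2/0.687 = 2.91; power = Φ(0.95) = 82.9%

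This rounds to the stated figure. With a t reference on 29 degrees of freedom it is 80.3%; with 15 villages in each arm it is 81.9% (normal). The implied CVs are 1/√8 = 0.35 and 1/√6 = 0.41, not 1.

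**2. Inputs as printed.** CV 1 gives V1 = 8² = 64 and V2 = 6² = 36:
- Effective sample sizes: 375/13 = 28.8 and 400/13 = 30.8
- SE = √(64 × 13/375 + 36 × 13/400) = √(2.219 + 1.170) = 1.841
- 2/1.841 = 1.09; power = Φ(−0.87) = 19.1%
- With t on 29 degrees of freedom: 18.2%

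**3. Ceiling.** As m grows without limit, DE/m tends to the ICC, so SE tends to √(64 × 0.5/15 + 36 × 0.5/16) = √(2.133 + 1.125) = 1.805. Power is then Φ(2/1.805 − 1.96) = 19.7%.

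**4. Other conventions, keeping CV 1 and ICC 0.5.**

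| Variant | Power |
|---|---|
| One-sided 5%, SD 8 and 6 | 28.8% |
| 15 villages in each arm | 18.8% |
| Common SD 8 / 7 / 6 | 16.0% / 19.6% / 25.0% |
| Common SD 6 and one-sided 5% | 36.0% |
| Ratio of means on the log scale | 19.8% |
| CV read as between-village variation in true means | 11–12% |
| CV read as variation in cluster size, SD equal to the mean | 11.8% |

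**5. ICC misprinted as 0.5 for 0.05, keeping CV 1.** DE = 1 + 24 × 0.05 = 2.2; SE = √(64 × 2.2/375 + 36 × 2.2/400) = 0.757; 2/0.757 = 2.64.
- Two-sided 5%: 75.2% (normal), 72.3% (t)
- One-sided 5%: 84.0% (normal), 82.5% (t)
- Common SD of 6, two-sided: 87.8% (normal), 85.6% (t)

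**6. Solving backwards (two-sided, normal).** To reach 83% with CV 1, the ICC would have to be about 0.034. To reach it with ICC 0.5, the CV would have to be about 0.37.

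**The case against.** The strongest reply is that the power is right and only a label is wrong. One change, variance equal to mean, recovers 82.9%, and the planned Poisson model has that variance as its nominal form. On that reading the sample size, design and analysis all stand, and the error is one misnamed term. This largely stands. A reader might infer from the arithmetic that the survey truly has 19% power, or that the sponsor overstated its power about fourfold. The documents do not support that: they show that the printed inputs and the printed result disagree, not which of them is wrong.

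A reader might equally infer that a mislabelled CV is proved. It is not. Alpha, sidedness and the test are unstated, and the method rests on a reference that is not reproduced. An ICC of 0.05 with CV 1 gives values on either side of 83%, depending on those choices. An ICC of 0.5 also lies well outside the 0.01 to 0.20 used in Table 4, although that table concerns a different outcome. A slipped decimal therefore remains possible. It is less likely because the plain two-sided version gives 75%, and coming close to 83% needs a further unstated choice.

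It can also be said that the survey serves descriptive aims (patient experience, motivators and inhibitors of screening) that do not depend on this figure, and that the primary outcome is untouched. Both are true, and they limit the importance of the point. They do not remove the contradiction, because the sentence presents 83% as following from its own listed assumptions.

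**Conclusion.** The stated power contradicts the assumptions printed beside it: about 19% (18% with t on 29 degrees of freedom) against 83%, with a ceiling of about 20% however many women are surveyed per village. This rests on two-sided alpha 0.05 and the usual design-effect formula. The gap does not depend on either choice: of the variants tried that keep CV 1 and ICC 0.5, the most favourable reaches 36%.

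At least one printed figure is therefore wrong. The most probable explanation is that a variance-to-mean ratio of 1 was described as a coefficient of variation of 1, in which case power is about 80–83%. A misprinted ICC is the less likely alternative. The point should be fixed, but it concerns a secondary outcome measured in a subsample and leaves the primary-outcome power in Table 4 unaffected.

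**What to change.** Go back to the original calculation, identify which input was misstated, correct it, and add the alpha, sidedness and test used, so that the stated power follows from the stated inputs.

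- If the variance was set equal to the mean, replace the CV statement with a variance-to-mean ratio of 1 (Poisson variance) and give power as about 80–83%, depending on whether a t or normal reference is used.
- If the ICC was misprinted, give the value used and the power that follows from it.
- If CV 1 and ICC 0.5 were both intended, restate power as about 19% and describe the knowledge comparison as estimation with confidence intervals, not as a powered test.

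The cost is one or two sentences in the Sample size section. None of these corrections changes recruitment, randomization or the conduct of the survey. Only the last changes how the knowledge result should be presented.

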### Randomization and blinding

The unit of randomization for the trial is the village. Randomization was performed in STATA by [name], stratified by sub-district (Mayuge and Buwaiswa) using a 1:1 allocation. Stratification was performed to balance the clusters around the two sub-districts that each includes health centres where VIA follow-up is taking place. Blinding of study staff, outcome assessors, or participants is not possible due to the spatial and temporal nature of intervention arms.

### Data collection methods

Primary trial data is captured through a survey of all participants at enrollment; a follow-up survey within 6 months of results; an audit of laboratory result logs; VIA screening logs; and referral and treatment logs at the participating facilities. All enrollment surveys are administered by a trained CHW in Lusoga or English based on the language of preference of the participant. The Core Plus module 1 (CPLUS1) from the Improving Data for Decision Making in Global Cervical Cancer Programs Toolkit-Part 2 (IDCCP) [24] is used to survey eligible women at enrollment. Modifications have been made to the tool to capture participants’ socio-demographic characteristics, preferences on integrated service delivery, and issues related to HIV and other health conditions in collaboration with local partners.

After completion of CCS follow-up and within 6 months of baseline recruitment, an additional subgroup of 775 participants are recruited by a research assistant to complete a knowledge retention and patient-experience survey to better understand inhibitors and facilitators to self-collected CCS behaviour. The CCS knowledge and patient experience survey design was primarily informed by the IDCCP CPLUS1 module [24] and the Organisation for Economic Co-operation and Development’s (OECD) patient-reported experience measures (PREMs) survey tools [25]. Questions regarding knowledge and awareness were taken from Mukama et al.’s [26] survey tool which was previously used to assess CCS knowledge among women in Eastern Uganda. Additional questions were developed to capture motivations for self-collection that are specific to intervention activities.

A supplementary survey is distributed to approximately 300 men in the Mayuge district who attend the community health meetings for arm 2. The men’s survey was designed using the IDCCP CPLUS1 module [24] to capture demographic information, their level of knowledge regarding HPV and cervical cancer and how that informs their attitudes about screening for their partners. It is administered by a CHW and will be conducted in a semi-private location. All responses to the men’s survey remain anonymous and no names are collected.

Cost and person-time data used for cost-effectiveness analysis is collected from the study’s financial records and by using customized survey tools completed at each health centre and through observations of both HPV and VIA screening during each study arm. An audit of the screening logs in each study designated health center is completed at the time of arm 1 recruitment start to estimate a cluster level measure of engagement in the VIA screening program prior to initiation of the study. Focus group discussions with participants who screen positive for HR-HPV and either complete or do not complete follow-up are conducted to evaluate the acceptability of screening and barriers and facilitators to engagement in care.

### Data management and monitoring

A customized data management tool was developed using Research Electronic Data Capture (REDCap) software [27]. Data is entered into the REDCap database by a trained data entry officer and reviewed monthly for completeness. A second reviewer (one of [name]) randomly selects 10% of the data for independent data quality verification. A data monitoring committee was not established for this trial as no major safety concerns are expected. Furthermore, there are no interim analyses planned and no stopping role. Weekly meetings are held with CHWs to monitor community response and collect information on any adverse or other unintended effects of trial interventions or conduct. Auditing of trial conduct occurs every 3 months by [name].

### Statistical analysis

#### Primary objective

Statistical analysis will be performed in R Statistical software using the clusterPower package [28] with an intention to treat approach. The primary outcome rate will be computed for each cluster and each study arm and ICCs calculated to assess cluster level variability prior to the primary analysis. The primary effectiveness measure will be compared between arms by estimating a mixed effect logistic regression model with cluster as a random intercept. The model will be adjusted for all known confounders at the individual and cluster level. There is no planned midpoint evaluation as no serious safety concerns are expected.

Apparent prevalence of HPV and STIs will be estimated in the study regions using trial data. Population prevalence of CIN2+ will be estimated based on this apparent prevalence using the reported sensitivity and specificity of the GeneXpert HPV test for this disease status (Table 5).

**Table 5 Tab5:** Diagnostic test characteristics for moderate and severe cervical lesions

	CIN2+	CIN3
Sensitivity	90.8%(84.7–95.0%)	92.3%(84.8–96.9%)
Specificity	42.6%(38.5–46.9%)	40.0%(36.1–44.0%)

Secondary outcomes compared between arms will be estimated in a similar manner. The effect of each study arm on HPV incidence is estimated using a multi-level logistic regression model as per the primary analysis. The effect of each study arm on CCS knowledge and patient experience will be estimated using a multi-level Poisson model, adjusted for the same individual and cluster level confounders with the addition of HPV status as an individual compounder and with person-time in follow-up as an offset.

Planned secondary analyses include estimating the group by arm interaction of HIV and other STI status on effectiveness of each CCS model. This will be done by adding an interaction term for each comorbidity and arm in the primary model. Temporal trends in HPV incidence and follow-up will be presented graphically.

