	What is the effect of screening model on CCS knowledge retention and follow-up uptake? Are women aware of cervical cancer and how knowledgeable are they about CCS?	Effectiveness (Individual level)	Mean CCS knowledge scores; cervical cancer awareness;	Quantitative analysis of survey data: multi-level Poisson model;
	What are the motivators or inhibitors of CCS behaviour among women?	Effectiveness (Individual level)	Primary and secondary factors that motivate self-collected CCS; Primary and secondary factors that motivate VIA follow-up; Primary and secondary factors that inhibit VIA follow-up; Perceived social support from CHWs;	Quantitative analysis of survey data: descriptive statistics; Chi squared; multivariate logistic regression; Qualitative analysis of open-ended survey questions: deductive thematic analysis
Secondary Objectives				
Cost and feasibility				
To evaluate the cost and feasibility of a community-based CCS program in a low resource setting.	Which CCS model is more cost-effective?	Implementation (Setting level)	Cost-effectiveness of each CCS model (total provider, laboratory, transportation, equipment, training, and treatment costs per arm)	Quantitative analysis of facility survey data: ICER and reduction in CCS over lifetime; sensitivity analysis
	What are the costs associated with a CCS program?	Implementation (Setting level)	Monetary and time costs of CHWs and health care providers; training costs; laboratory costs; treatment costs; patient time costs;	Process evaluation: Narrative assessment/quantitative analysis of study logs: Descriptive statistics - univariate analysis (frequencies)
Best Practices for integrated community care				
To identify the barriers and facilitators of implementation, implementation reach, and fidelity for each model of CCS.	What are patients’ preferences for integrated service delivery? (barriers/facilitators of implementation)	n/a	Patients’ preferences for integrated service delivery	Quantitative analysis of survey data: Chi squared; multivariate logistic regression
	What is the acceptability of a community-based CCS program among participants? (barriers/facilitators of implementation)	Effectiveness (Individual level)	Patient-reported experiences with a community-based CCS program	Quantitative analysis of survey data: Descriptive statistics with time from sample collection to patient experiences survey as offset; Qualitative analysis of open-ended survey questions: deductive thematic analysis

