	What were the CCS program inputs? (Implementation reach)	Implementation (Setting level)	Total program inputs (financial, human, administrative, equipment resources)	Process evaluation. Narrative assessment/quantitative analysis of study logs: Descriptive statistics - univariate analysis (frequencies)
	What was the reach of the program? (Implementation reach)	Reach (Individual level)	Participation at each level of the pathway to care; stakeholder engagement; Survey participation; sociodemographic characteristics of participants	Process evaluation. Quantitative analysis of survey, study log, and clinical data: Descriptive statistics - univariate analysis (proportion, frequency, mean); Chi squared; T-test;
	How many participants were lost to follow-up? (fidelity)	Maintenance (Individual level)	Attrition at each level of the pathway to care	Process evaluation. Per-protocol analysis; Quantitative analysis of survey, study log, and clinical data: Descriptive statistics - univariate analysis (frequency); sociodemographic characteristics of those lost to follow-up
	Was the CCS program implemented as intended? (fidelity)	Implementation (Setting level)	Planned vs actual intervention components (e.g. number of training sessions, number of specimens transported and tested, etc.)	Process evaluation. Quantitative analysis of study logs and clinical data: Descriptive statistics - univariate analysis (mean, frequency)
	How successful was VIA training and quality monitoring during the trial? (fidelity)	Implementation (Setting level)	Detection rates of CIN2+ lesions over time; adverse and serious adverse events; Themes related to health care workers experiences;	Quantitative analysis of clinical data: descriptive statistics - univariate analysis (frequency); qualitative analysis; qualitative analysis of FGD data: deductive thematic analysis
	How acceptable and feasible is the HPV screen and treat approach to women and health workers? (barriers/facilitators of implementation)	Implementation (Individual level)	Treatment rate vs. VIA + rate; patient reported experience measures from treatment; themes related to health care workers experiences	Quantitative analysis of clinical data: descriptive statistics - univariate analysis (frequency); qualitative analysis; qualitative analysis of FGD data: deductive thematic analysis

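### Table 2 lists tests with no cluster term for programme reach, which Table 1 compares between arms, and the primary model does not name the stratification factor.

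*Protocol article*

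**What the plan says.** **Design.** Under Randomization and blinding, the protocol article states "The unit of randomization for the trial is the village", with allocation "stratified by sub-district (Mayuge and Buwaiswa) using a 1:1 allocation". The reason given is "Stratification was performed to balance the clusters around the two sub-districts that each includes health centres where VIA follow-up is taking place". The stratum is therefore tied to where the primary outcome, attendance for VIA, takes place. Under Sample size, "Sample size for the study was restricted to the 31 villages in the region available for randomization". The survey subsample takes "25 participants from each cluster to total 375 participants from arm 1 and 400 from arm 2", which implies 375/25 = 15 and 400/25 = 16 villages.

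**Primary and named secondary analyses.** Under Statistical analysis, Primary objective, the arms are compared by "estimating a mixed effect logistic regression model with cluster as a random intercept", with adjustment for known confounders of women and of villages. Sub-district is not named. HPV incidence gets a multi-level logistic model. Knowledge and patient experience get a multi-level Poisson model.

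**Table 2 (Study outcomes).** The reach row covers participation at each step of the care pathway and lists "Descriptive statistics - univariate analysis (proportion, frequency, mean); Chi squared; T-test". The row on preferences for integrated services lists "Quantitative analysis of survey data: Chi squared; multivariate logistic regression". The row on motivators and inhibitors lists the same two methods after descriptive statistics. None of the three mentions cluster.

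**Table 1 (Intervention).** Screening uptake, and attendance at each level of the care pathway, are given as indicators compared between arms.

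**The concern.** Pathway participation in the reach row of Table 2 is essentially the quantity that Table 1 compares between arms, and VIA attendance is one of its steps. As written, attendance is analysed with a village random intercept under Statistical analysis and can be analysed with a test that treats every woman as independent under Table 2. Because villages were randomised, the second route understates the standard error of any difference between arms. Uptake and reach are among the results meant to inform national scale-up, so a false signal there matters even though it is not the primary outcome.

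The stratum raises a different issue. Sub-district was chosen for stratification because it is linked to the follow-up clinics. If attendance differs between sub-districts and the model has no term for it, that difference goes into the between-village variance and makes the arm comparison less precise. A rule to adjust for known confounders does not clearly bring the stratum in, because a factor balanced by design need not be regarded as a confounder.

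**Working it through.** **Step 1. Reproduce the plan's own power.** Inputs from Sample size: 15 villages per arm, 70 women each, 20% baseline rate, Table 4 ICCs. A two-sided 5% level is assumed, since the article states none. Effective sample size per arm = 15 × 70 / (1 + 69 × ICC), put into the usual normal-approximation power for two proportions.

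| ICC | Effective n per arm | Computed power, 20% vs 30% | Table 4 |
|---|---|---|---|
| 0.01 | 1050/1.69 = 621 | 98.3% | 98% |
| 0.05 | 1050/4.45 = 236 | 71.0% | 71% |
| 0.10 | 1050/7.90 = 133 | 46.9% | 47% |
| 0.20 | 1050/14.8 = 71 | 27.8% | 28% |

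The 20-point and 30-point columns also agree, within about one point. The planned power therefore already allows for clustering.

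**Step 2. Error of a between-arm test that ignores village.** With design effect DE = 1 + (m − 1) × ICC, the test statistic has a null standard deviation of about √DE, so the true type I error of a nominal 5% test is 2 × [1 − Φ(1.96/√DE)].

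| ICC | DE, m = 70 | True error | DE, m = 25 | True error |
|---|---|---|---|---|
| 0.01 | 1.69 | 13% | 1.24 | 8% |
| 0.05 | 4.45 | 35% | 2.20 | 19% |
| 0.10 | 7.90 | 49% | 3.40 | 29% |
| 0.20 | 14.8 | 61% | 5.80 | 42% |

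Example: ICC 0.05, m = 70 gives √4.45 = 2.11; 1.96/2.11 = 0.929; two-sided tail 0.353. A beta-binomial simulation of 15 against 16 villages at a 20% rate (20,000 runs per cell) agrees with every cell to within half a percentage point. The m = 70 column suits measures taken on all participants, such as reach. The m = 25 column suits the follow-up survey subsample.

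**Step 3. Effect of leaving out the stratum.** The article gives no sub-district difference, so a gap of 0, 10 or 20 percentage points is assumed. Village rates were simulated (20,000 runs per setting; 15 and 16 villages of 70 women, split about evenly between sub-districts; ICC taken within sub-district) and analysed by village-level linear regression with a t reference, with and without a sub-district term. This approximates the planned mixed logistic model.

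Power for 20% vs 30%, without / with the stratum:

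| ICC | No gap | 10-point gap | 20-point gap |
|---|---|---|---|
| 0.01 | 98% / 98% | 95% / 98% | 76% / 98% |
| 0.05 | 70% / 70% | 65% / 70% | 49% / 72% |
| 0.10 | 47% / 46% | 44% / 47% | 35% / 49% |
| 0.20 | 27% / 27% | 27% / 28% | 24% / 29% |

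Type I error at ICC 0.05 is 4.7%, 2.9% and 0.6% without the stratum at gaps of 0, 10 and 20 points, and about 5% with it. Omission makes the test conservative.

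**The case against.** The strongest reply has several parts.

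- **A reader might infer that the analyses ignore the randomised design. The article does not support that.** The primary model has a village random intercept, the three secondary outcomes listed as compared between arms are analysed by multi-level models, and the risk difference in Table 2 is adjusted for cluster. This part of the reply stands in full.
- **Table 2 does not say that its chi-squared and t-tests compare arms.** This stands for motivators and preferences, where the tests may serve other comparisons. It is weaker for reach, because Table 1 declares pathway attendance and uptake to be between-arm indicators. Nor does the missing cluster term look like shorthand, since other rows of the same table do specify clustering.
- **Sub-district may come in as a cluster-level confounder.** The covariate rule is open-ended, and the planned audit of earlier VIA engagement could absorb part of a clinic difference. So the stratum is not named, which is different from being excluded.
- **A reader might infer a fault in the lack of a small-sample reference for 31 villages.** The article fixes no reference distribution, and this is detail usually left to the analysis plan. The effect is small: 2 × P(T on 29 df > 1.96) = 0.060 against 0.05. It is not part of this point.
- **A reader might apply the survey's ICC of 0.5 in Step 2.** That value belongs to the knowledge score, which is analysed by a multi-level Poisson model, so it is not used here.

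**Conclusion.** The point holds in two limited parts.

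The reach row conflicts with Table 1 and with the multi-level approach under Statistical analysis. If its tests, or those listed for motivators and preferences, are used between arms, true type I error is roughly three to twelve times nominal at 70 women per village over the protocol's own ICC range (13/5 to 61/5). This touches process and uptake comparisons only. It rests on a 5% two-sided level, equal village sizes, and the Table 4 ICCs applying to these measures.

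Not naming the stratum is a matter of power, not validity. At ICC 0.05 the loss for a 10-point effect is nil with no sub-district gap, about 5 points with a 10-point gap and about 23 points with a 20-point gap. It shrinks at the highest ICC. The gap is an assumption, and the documents give no figure for it. Since Table 4 offers only 71% in this cell, there is little to spare. The change is worth making, but neither part undermines the primary comparison.

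**What to change.** Name sub-district as a fixed effect in the primary model and in the secondary models that compare arms.

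In Table 2, state which rows compare arms. For those, replace chi-squared, t-test and logistic regression without a cluster term by the village random-intercept model already described under Statistical analysis, or by a test on village-level summaries. Rows that are purely descriptive can stay as they are once labelled so.

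The cost is a change of wording and one degree of freedom, with no new data. Intervals for process comparisons will be wider, and some differences that would have looked significant may not remain so.
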